#### Modified Ashworth Scale (MAS)

The MAS is an instrument used to evaluate the spasticity (i.e. grading the resistance encountered during such passive muscle stretching) [47, 48]. The grades of spasticity are 0 (normal muscle tone), 1 (slight increase in muscle tone, when move a limb), 2 (more marked increase in muscle tone, but limb easily flexed), 3 (considerable increase in muscle tone), and 4 (limb rigid in flexion or extension) [47].

#### Socio-demographic questionnaire (SDQ)

The SDQ will be used to collect personal, socio-environmental, and clinical information. It will also determine information used to evaluate participants’ eligibility criteria. Our research center standardized this qualitative instrument, but a pilot test will be conducted to identify possible necessary adjustments to this questionnaire. In summary, this scale will be used as a sample description and as an eligibility criterion.

#### Scale of Mini-Mental State Examination

The MMSE assesses the mental state of the individuals assessed [49, 50]. The maximum score is 30 and there are two domains. The first tests for vocal responses, which covers orientation, memory, and attention (maximum of 21 points). The second tests for the ability to name objects, obey verbal and written commands, write a sentence spontaneously, and copy a complex polygon (maximum of nine points) [50, 51]. In Brazil, Bertolucci et al. [52] translated the MMSE. They found that the educational level of participants influenced their total score on the MMSE. As a result, the authors have proposed different cut-offs for the diagnosis of cognitive decline. The suggested cutoff points were 13 for illiterates, 18 for low and middle school, and 26 for high school. We will use this scale as an eligibility criterion.

#### Hamilton Rating Scale for Depression

The HAM-D is used to identify depression and contains 17 items plus four additional variables (diurnal variation, derealization, paranoid symptoms, and obsessive symptoms) [53]. Hamilton has not established a cut-off point, but in clinical practice scores higher than 25 points characterize severely depressed patients; scores in the range of 18–24 indicate moderate depression; and scores in the range of 7–17 indicate mild depression [54]. We will use this scale as an eligibility criterion.

#### Electroencephalogram

EEG provides a measurement of brain electrical activity (i.e. the amount of synaptic activity synchronized) recorded from scalp electrodes [55]. Applications of EEG can be used in identification of nature, type, and severity of epileptiform activity [56]. In this study, the EEG will be used to identify individuals with epilepsy or brain-activity patterns that may indicate possible underlying seizures. Therefore, this exam will serve only as an eligibility criterion.

#### Neurological examination (NE)

Clinical data collection will be achieved via qualitative standardized NE. This instrument consists of four parts: a history of the lesion and clinical symptoms; sensory and motor evaluation; functional activities; superficial and deep reflections.

### Statistical analysis

#### Sample size

The sample size was calculated using statistical software (GPower 3.1.5) [57] on the main outcome measure (i.e. the motor score). This calculation was based on data from one study with a group of SCI individuals that received high-frequency rTMS at a frequency of 5 Hz on the vertex, which related to an improvement in clinical measures of the motor score [24]. The power was 0.80; the alpha was 0.05, the effect size was 0.65 (Cohen’s *d*). The sample estimation indicated that 14 participants would be necessary (i.e. seven per group). With an adjustment to allow for a dropout rate, we will recruit 20 participants.

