### Study design

A double-blinded randomized controlled crossover trial will be conducted and all participants will undertake rTMS-active and sham. Group 1 will start with five sessions of rTMS-active. After two weeks, this group will be reallocated to five sessions with rTMS-sham. In contrast, group 2 will do the opposite protocol (participants will start allocated to five sessions of rTMS-sham, and after a two-week washout period will be reallocated to five sessions of rTMS-active). The two-week washout period has been used in some studies [24, 27] and was shown to be enough to reset the effects of the first five sessions, considering that the motor effects of the rTMS in individuals with iSCI are sustained for 1 h [24] to two weeks [14] and that spasticity effects endure for one week [16, 23]. Figure 1 summarizes the planned experimental design. This research protocol follows the SPIRIT recommendations. For the SPIRIT Checklist see Additional file 1 and for the SPIRIT Figure see Fig. 2. Table 1 provides an overview of the trial characteristics, based on the WHO Trial Registration Data Set.

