#### Data analysis

The analysis will follow a pre-specified analysis plan, based on comparing the groups as randomized (intention-to-treat). All data will be presented as mean ± standard deviation and summarized in frequency tables. We will use Microsoft Office Excel for Windows (version 2013) to store the data and the Statistical Package for Social Sciences (SPSS-IBM®) version 21 for Windows to perform statistical analysis. The normality and homogeneity of all variables (i.e. primary and secondary outcomes) will be tested with the Shapiro–Wilk and Levene’s test, respectively. For non-parametric data, the Friedman test will be used followed by the Wilcoxon post hoc test. We will use the ANOVA two-way (2 × 4) for the inferential statistic of the parametric data, with Tukey’s post hoc tests. Significance level will be set as α ≤ 0.05 and the effect size will be calculated by eta-squared (*ŋ*
^*2*^).

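### The 14 participants in the sample size paragraph do not follow from d = 0.65, alpha 0.05 and power 0.80; a two-sided paired test on those inputs needs 21 completers

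*Protocol article*

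**What the plan says.** The protocol article, Sample size, names the software ("The sample size was calculated using statistical software (GPower 3.1.5") and gives the inputs: "The power was 0.80; the alpha was 0.05, the effect size was 0.65", the last labelled as Cohen's d. From these it states: "The sample estimation indicated that 14 participants would be necessary (i.e. seven per group". It then adds: "With an adjustment to allow for a dropout rate, we will recruit 20 participants". The dropout rate is not given; going from 14 to 20 implies 1 − 14/20 = 30%.

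The paragraph does not name the test that was powered, whether it is one- or two-sided, which SD standardises d, or any within-person correlation.

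Study design describes the trial as follows: "A double-blinded randomized controlled crossover trial will be conducted and all participants will undertake rTMS-active and sham". Group 1 and group 2 are the two orders of treatment. Data analysis plans the parametric test: "We will use the ANOVA two-way (2 × 4) for the inferential statistic of the parametric data", with "Significance level will be set as α ≤ 0.05". The four levels match the assessments before and after each of the two periods (Fig. 1 legend).

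**The concern.** The paragraph gives an effect size, an alpha, a power and a resulting number, so the result can be checked. In a two-period crossover the ordinary reading of a d of 0.65 is a standardised within-participant difference tested with a paired test, and 14 is too few for that at 80% power.

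The plan treats 14 completers as enough, because recruiting 20 is explained as an allowance for dropout. The Dropout criteria withdraw anyone who misses a session or changes rehabilitation, so ending near 14 is possible. On the two-sided paired reading, a true effect of 0.65 would then be missed about 39% of the time, not the 20% that the paragraph implies. The Background presents the trial as a response to inconsistent evidence, so a null result read against a stated 80% power would carry more weight than it should.

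**Working it through.** **Inputs from the article.** Alpha 0.05, power 0.80, d = 0.65, N = 14 (7 + 7), 20 recruited. Sidedness, the SD behind d and the within-person correlation ρ are not stated, so each is varied below. Power comes from the exact noncentral t or F distribution.

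**1. Attempt to reproduce 14 with t-tests on the stated inputs**

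*Paired test, d on the active-minus-sham difference.* Noncentrality = d√N, df = N − 1.
- N = 14: 0.65 × √14 = 2.432; two-sided critical t (13 df) = 2.160; power 0.614.
- N = 20: 0.65 × √20 = 2.907; critical t (19 df) = 2.093; power 0.787.
- N = 21: 0.65 × √21 = 2.979; critical t (20 df) = 2.086; power 0.809. This is the smallest N that reaches 0.80.
- Period-adjusted (df = N − 2): 0.608 at 14, 0.785 at 20; 22 needed if the sequences are balanced.
- One-sided: 0.745 at 14 and 0.876 at 20; 17 needed (0.821).

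*Parallel groups, n per group.* Noncentrality = d√(n/2), df = 2n − 2.
- n = 7: 0.65 × √3.5 = 1.216; two-sided power 0.202.
- n = 10: 0.280.
- n = 39: 0.809, the smallest that reaches 0.80. One-sided, 30 per group.

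None of these gives 14.

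**2. Readings that need an input the article does not state**

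*(a) d on the between-subject SD.* The paired effect is then dz = d/√(2(1 − ρ)). Two-sided paired power at N = 14:

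| ρ (assumed) | dz | Power at 14 | Power at 20 |
|---|---|---|---|
| 0 | 0.460 | 0.357 | 0.497 |
| 0.3 | 0.549 | 0.477 | 0.645 |
| 0.5 | 0.650 | 0.614 | 0.787 |
| 0.68 | 0.813 | 0.802 | 0.931 |
| 0.7 | 0.839 | 0.827 | 0.945 |
| 0.8 | 1.028 | 0.944 | 0.992 |

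Fourteen is enough once ρ is about 0.68 or more.

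*(b) 2 × 4 repeated-measures ANOVA, group-by-time interaction.* λ = f²·N·m/(1 − ρ), with m = 4 and df 3 and 3(N − 2).
- f = d/2 = 0.325, ρ = 0.5: λ = 0.325² × 14 × 4/0.5 = 11.83; power 0.788 at 14 and 0.930 at 20; 15 needed, or 16 if balanced.
- f = d/√8 = 0.23, which applies if only the post-active score shifts by d, ρ = 0.5: power 0.465 at 14 and 0.646 at 20; 28 needed. With ρ = 0.8, power at 14 is 0.878.

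*(c) 2 × 4 repeated-measures ANOVA, between-groups effect.* λ = f²·N·m/(1 + (m − 1)ρ), df 1 and N − 2.
- 0.65 entered as Cohen's f, ρ = 0.5: at N = 12, λ = 8.112 and power 0.728; at N = 14, λ = 0.65² × 14 × 4/2.5 = 9.464 and power 0.806. The smallest N is exactly 14.
- The same setting with f = d/2 = 0.325: power 0.294 at 14; 49 needed, or 50 if balanced.

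Reading (c) matches the 14 and the 2 × 4 layout, but f = 0.65 corresponds to d = 1.3. The effect it tests is also the difference between the two sequence groups, and both of those receive active and sham.

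**The case against.** The strongest reply is that the article says only Cohen's d and leaves the standardising SD open. If d is on the between-subject SD and repeated motor scores correlate at about 0.7, a two-sided crossover test needs exactly 14 and has 83% power. The protocol's own 2 × 4 interaction, with f = 0.325 and ρ = 0.5, comes within about one percentage point of 80% at 14. This stands in part. A reader might infer from the t-test results that no reading of the design supports 14, and the document does not bear that out. But each rescue needs a correlation that the article does not give, and reading (a) runs from 36% to 94% over ρ from 0 to 0.8. The stated power would rest on an input that is not there.

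A reader might also infer that even 20 completers are too few. That holds for the two-sided paired reading only by about one point (78.7%). With 20 completers a one-sided paired test has 88%, reading (a) at ρ = 0.7 has 94%, and reading (b) with f = 0.325 has 93%. It is not a fact about the trial as a whole.

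Nor is the mention of seven per group a sign that a parallel design was powered. The two groups are the randomised sequences, and 14 participants are seven per sequence.

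Finally, the exact match in (c) may suggest that 0.65 was entered as f and reported as d. It is a possible origin. The article does not name the test family, so it is not shown.

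**Conclusion.** Wrong as written. The stated d, alpha and power do not give 14 in a paired, period-adjusted or parallel t-test. With d taken as the standardised active-minus-sham difference and a two-sided 5% test, 14 completers give about 61% power, 20 give about 79%, and 21 are needed. The one-sided paired requirement is 17, and the parallel one is 39 per group.

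The 61% and 79% rest on that scaling of d, which is equivalent to ρ = 0.5 if d is on the between-subject SD. What is established is that the number cannot be reproduced without an unstated input. It is not established that the trial lacks 80% power on every defensible reading.

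**What to change.** Keep the 20 participants and rewrite the sample size paragraph in one of two ways.

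- If the paired test is meant: *For a two-sided 5% paired test with d = 0.65 on the within-participant active-minus-sham difference, power is about 61% with 14 completers and 79% with 20 (21 needed for 80%).*
- If another calculation was meant: state the test and the effect it tests, the sidedness, the SD behind d and the assumed within-person correlation, and show that together they give 14. If 0.65 was entered as Cohen's f for the between-groups effect, replace the calculation, because that effect is not active versus sham.

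The count per group can stay, better worded as seven per sequence.

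The cost is one rewritten paragraph and no extra participants. On the first option the stated power becomes less favourable.

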#### Data analysis

The analysis will follow a pre-specified analysis plan, based on comparing the groups as randomized (intention-to-treat). All data will be presented as mean ± standard deviation and summarized in frequency tables. We will use Microsoft Office Excel for Windows (version 2013) to store the data and the Statistical Package for Social Sciences (SPSS-IBM®) version 21 for Windows to perform statistical analysis. The normality and homogeneity of all variables (i.e. primary and secondary outcomes) will be tested with the Shapiro–Wilk and Levene’s test, respectively. For non-parametric data, the Friedman test will be used followed by the Wilcoxon post hoc test. We will use the ANOVA two-way (2 × 4) for the inferential statistic of the parametric data, with Tukey’s post hoc tests. Significance level will be set as α ≤ 0.05 and the effect size will be calculated by eta-squared (*ŋ*
^*2*^).

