**Fig. 1 Fig1:**
[figure not shown]
*Flowchart* for the rTMS study protocol. The participants will be selected and the eligibility assessment will be applied. They will then be randomized and allocated to group 1 (starting with rTMS-active) or group 2 (starting with rTMS-sham). Five sessions of rTMS-active and sham will be applied to participants in each group over one week, with a washout period (two weeks). Assessments will be before and after each intervention period (i.e. sham and active) using the motor and sensory scales, spasticity scale, and surface electromyography

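### With four repeated assessments, the Friedman test and a repeated-measures 2 × 4 ANOVA use only complete sets, so without imputation they do not deliver the intention-to-treat analysis the plan states

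*Protocol article*

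**What the plan says.** The Data analysis section sets the principle: "The analysis will follow a pre-specified analysis plan, based on comparing the groups as randomized (intention-to-treat)". The same section then names the tests. For data judged normal: "We will use the ANOVA two-way (2 × 4) for the inferential statistic of the parametric data". Otherwise: "For non-parametric data, the Friedman test will be used followed by the Wilcoxon post hoc test". The software is SPSS ("version 21 for Windows to perform statistical analysis").

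Two other places fix the data structure. Study design: "A double-blinded randomized controlled crossover trial will be conducted and all participants will undertake rTMS-active and sham". Fig. 1 caption: "Assessments will be before and after each intervention period". With two intervention periods, that makes four scores per person, all within the same person.

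Losses are foreseen. The Dropout criteria section withdraws people for absence, a missed session or a change of rehabilitation. The Sample size section arrives at 14 and adds: "With an adjustment to allow for a dropout rate, we will recruit 20 participants". It gives no dropout rate. Nothing in the article says how a participant with a missing assessment is handled.

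**The concern.** A Friedman test ranks the four scores within each participant and needs the whole block. A classical repeated-measures ANOVA drops any participant with an empty cell. A participant with valid before and after scores from period 1 who then leaves would therefore be absent from the main test, although those scores are on file.

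Two things are at stake in a trial of 20. One is precision, because collected scores go unused. The other is bias: if leaving depends on how the participant fared in period 1, the completers are a selected group. The period-1 result that drives the selection has been observed and could be used to correct for it. Recruiting 20 to keep 14 protects power but does nothing about bias.

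**Working it through.** **1. The plan's own figures.** 14/(1 − 0.30) = 20, so the enlargement is equivalent to losing up to 6 of 20 (30%). The figure of 14 cannot be reproduced with certainty, because the test and the correlation are not stated. With d = 0.65 and 80% power, a paired t-test needs 21 (two-sided) or 17 (one-sided). An independent t-test needs 39 or 30 per group. A repeated-measures ANOVA interaction with 2 groups, 4 measurements, f = 0.65/2 = 0.325 and an assumed correlation of 0.5 needs 15 (16 if groups are equal) and has power 0.788 at 14. Other correlations move this widely (28 at 0, 10 at 0.7). It is therefore only weak support for reading the 2 × 4 ANOVA as repeated-measures; the crossover with four scores per person is the stronger reason.

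**2. Do the tests need complete sets?** Checked in Python, not SPSS. The Friedman test returned no result with one value missing, and a repeated-measures ANOVA with one score removed was refused as unbalanced.

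**3. What leaves the analysis.** If 6 of 20 leave after period 1, 80 − 12 = 68 scores are collected and 14 × 4 = 56 are analysed, so 12 valid scores go unused. If instead each assessment is missing independently with an assumed chance of 5%, expected complete cases are 20 × 0.95⁴ = 16.3.

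**4. Information lost.** Assumptions: 7 completers and 3 period-1-only participants per sequence; period change scores with variance 1 and between-period correlation r; treatment, period and sequence in the model. Within one sequence, the variance of the period-1 minus period-2 mean is

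- complete cases: 2(1 − r)/7
- all data: (1 − r)²/10 + (1 − r²)/7

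The ratio of the first to the second simplifies to 20/(17 + 3r).

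| r | Ratio | Gain | Completers it is worth (14 × ratio) |
|---|---|---|---|
| 0 | 20/17.0 | 17.6% | 16.5 |
| 0.3 | 20/17.9 | 11.7% | 15.6 |
| 0.5 | 20/18.5 | 8.1% | 15.1 |
| 0.9 | 20/19.7 | 1.5% | 14.2 |

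Without the sequence term the gains would be 21.4%, 15.0%, 10.7% and 2.1%. The smaller figures belong to the model recommended here.

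**5. Bias of complete cases.** Assumptions: the chance of leaving is logistic in the period-1 change, higher after a poor change, with 30% leaving overall; d = 0.65 is read as the standardised within-person difference, so the planned effect is 0.65 × √(2(1 − r)). Let δ be the upward shift, in SD, of the completers' mean period-1 change in a sequence. Then bias = ½(1 − r)(δ active-first − δ sham-first). The δ values come from numerical integration over a normal distribution.

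| r | Slope per SD | δ active-first, sham-first | Bias (SD) | Share of planned effect |
|---|---|---|---|---|
| 0.5 | 0.5 | 0.128, 0.158 | −0.008 | about 1% of 0.65 |
| 0.5 | 1 | 0.208, 0.298 | −0.023 | about 3% of 0.65 |
| 0.5 | 2 | 0.280, 0.470 | −0.047 | about 7% of 0.65 |
| 0 | 2 | 0.242, 0.507 | −0.13 | about 14% of 0.92 |
| 0.9 | 2 | 0.332, 0.418 | −0.004 | under 2% of 0.29 |

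For scale, the complete-case standard error at r = 0.5 is √((1 − r)/7) = 0.27. In simulation, the estimate from all data was unbiased to within 0.01.

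**The case against.** The strongest reply is that the article never says incomplete participants are excluded. It refers to an analysis plan that is not shown, and missing-data rules commonly sit there. Any stated imputation would let both named tests include all 20. This stands: the loss is conditional on no imputation, and the absence of an imputation rule from the article is not the point made here. What remains is that the article itself fixes tests that cannot use incomplete participants unaided.

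A reader might go further and infer that the plan discards data and contradicts its own intention-to-treat statement. The document does not support that. It explains intention-to-treat as comparing groups as randomised, and omitting an incomplete record moves nobody out of their randomised sequence. The tension is with including everyone randomised, which is how the term is ordinarily read but is not spelled out.

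Two further points stand. The words repeated-measures are not in the text; an ordinary between-subject ANOVA would not drop whole participants, but it would treat each person's four scores as independent and would need replacing for that reason. And the Wilcoxon post hoc test needs only pairs, so a period-1 leaver could still enter one of those comparisons, though not the Friedman test that precedes them.

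Finally, 20 recruits already cover six losses. Under the step 1 assumptions, power falls from 0.93 at 20 to 0.79 at 14, close to the planned 0.80. That answers the power question, not the bias question.

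**Conclusion.** The concern holds in conditional form. Used as named and without imputation, the main tests reduce a stated intention-to-treat analysis to complete cases, in a plan that expects participants to be lost.

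The size is modest. The information gain of about 18% down to under 2% is for the case in which the whole allowance is used up, all after period 1 and evenly by sequence; fewer or earlier losses would make it smaller. The bias pulls the active-minus-sham estimate towards zero if people tend to leave after a poor period-1 change. It depends on an assumed departure slope and correlation, neither of which the document gives: about 1% to 7% of the planned effect at correlation 0.5 (slope 0.5 to 2 per SD), up to about 15% at correlation 0, and small beside the standard error at correlation 0.5. The change is still worth making, because it is cheap and the better method uses data already collected.

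**What to change.** For the primary motor score and the other approximately continuous scores, replace the 2 × 4 ANOVA and Friedman test with a linear mixed model. The outcome is the change in each period, or the post-period score adjusted for the pre-period score. Treatment, period and sequence are fixed effects and participant is a random effect. Fit it to every available period of every randomised participant. The outcome should not be all four raw scores with treatment coded by period, because that would count pre-period scores as treated.

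Keep the complete-case or rank-based analysis as a sensitivity analysis, and use the rank-based analysis for the ordinal spasticity grade. State in the intention-to-treat sentence which participants the model includes; someone with no complete period still contributes no change score.

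Cost: revised wording and slightly more analysis work, with no new patients, visits or data. The named software can fit such a model. The small downside is reliance on scores being missing at random, which is a weaker assumption than the complete-case tests need.

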#### ASIA – motor score

The International Standards for Neurological Classification of Spinal Cord Injury (ISNCSI) is a medical examination from which part of the ASIA motor score is derived [42]. It uses a test of the strength of ten key muscles on each side of the body (e.g. elbow flexors, wrist extensors, hip flexors, quadriceps, dorsi flexors). The score ranges from 0 (no contraction) to 5 (normal resistance) through a full range of motion. A total possible score of 50 for the upper extremities (UE) and 50 for the lower extremities (LE) may be obtained [42].

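### Shapiro–Wilk and Levene results decide whether the primary motor-score analysis is a 2 × 4 ANOVA or a Friedman test, so the primary hypothesis depends on a screening result

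*Protocol article*

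**What the plan says.** The Data analysis section of the protocol article gives a rule in three steps.

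- Screening: "The normality and homogeneity of all variables (i.e. primary and secondary outcomes) will be tested", by Shapiro–Wilk for normality and Levene for homogeneity.
- If screening fails: "For non-parametric data, the Friedman test will be used followed by the Wilcoxon post hoc test".
- If it passes: "We will use the ANOVA two-way (2 × 4) for the inferential statistic of the parametric data", followed by Tukey comparisons.

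The same section opens with a commitment: "The analysis will follow a pre-specified analysis plan, based on comparing the groups as randomized (intention-to-treat". It closes with the error rate: "Significance level will be set as α ≤ 0.05".

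Other sections supply the context. Under Study design, every participant receives both active and sham stimulation. The Fig. 1 caption places assessments before and after each of the two periods, which makes four. Table 1 and Primary outcomes define the primary outcome as a change in motor score. The ASIA motor score is bounded: "A total possible score of 50 for the upper extremities (UE) and 50 for the lower extremities (LE) may be obtained". The inclusion criteria admit several causes of incomplete injury and do not restrict injury level or baseline severity beyond incompleteness.

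**The concern.** In a crossover trial the treatment comparison is made within participants. The normality that matters is therefore that of the active-minus-sham difference, or of the model residuals. The section screens the outcome variables and mentions neither differences nor residuals. Screening the wrong quantity can divert the analysis for reasons unrelated to the validity of the treatment comparison, such as a mix of mild and severe injuries.

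The diversion would be less serious if both branches tested the same hypothesis, but they do not. Friedman is a one-way rank test across related measurements. It cannot separate treatment from period, and it does not use the randomised sequence. A screening result could therefore replace the promised comparison of randomised groups with a different one.

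**Working it through.** **Inputs from the article.** N = 20 recruited and 14 required, 1:1 allocation, four assessments, α = 0.05, planning effect d = 0.65. The article gives no figure for the behaviour of the screening rule, so there is none to reproduce. The two sample sizes are linked by 14 / (1 − 0.30) = 20. The derivation of 14 is a separate matter and is not needed here.

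**Assumptions.** The article gives no SDs. Baseline motor scores were taken as normal (SD 20), clustered (two groups centred at 50 and 90) or skewed (exponential below the ceiling). Visit-to-visit error was exactly normal with SD 3. The between-visit correlation with normal baselines is then 20² / (20² + 3²) = 400/409 = 0.98. Lower correlations were also tried. A switch was counted when any Shapiro–Wilk test gave p < 0.05. The parametric branch was represented by a crossover t-test, because the article does not say what the 2 and the 4 stand for.

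**1. Switching by chance (truly normal data).** If the tests were independent, the chance of at least one failure would be 1 − 0.95⁴ = 18.5% for four tests and 1 − 0.95⁸ = 33.7% for eight. Correlated visits give less:

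| Correlation | Four pooled tests (n = 20) | Eight group-by-visit tests (n = 10) |
|---|---|---|
| 0.80 | 16.8% | 32.1% |
| 0.90 | 14.4% | 28.8% |
| 0.95 | 11.6% | 22.8% |
| 0.98 | about 10% | about 20% |
| 0.985 | about 8% | about 18% |

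At 0.98, adding Levene raises the last column to 24%–25%.

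**2. Switching because patients differ.** Write the active-minus-sham change as D = (post − pre, active) − (post − pre, sham). A participant's own level appears in all four terms and cancels. Visit scores keep it.

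| Baselines | Visit scores trigger switch, N = 14 | N = 20 |
|---|---|---|
| Skewed | about 69% | about 86% |
| Clustered | 99% | over 99.9% |

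In the same runs D fails Shapiro–Wilk in 4%–5%. The size depends on the assumed mix. Illustrative total scores with 30%–70% paraplegia give raw-score failure in 8%–29%, against 6%–7% for differences.

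**3. Type I error.** With no time trend, the test chosen by the gate rejects a true null in 4.1%–5.4% of runs.

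Now let scores drift by 0.5 error SD per visit with no treatment effect. Number the visits 0 to 3. Group 1 has active at visits 0 and 1 and sham at 2 and 3; group 2 has the reverse. The average visit index by condition is:

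- pre-active (0 + 2)/2 = 1
- post-active (1 + 3)/2 = 2
- pre-sham (2 + 0)/2 = 1
- post-sham (3 + 1)/2 = 2

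Both post conditions thus sit one step (0.5 error SD) above both pre conditions, and Friedman reads this as a difference. In D each change contains one step, so the drift cancels.

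Rejection rates at N = 20 under this drift:

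| Procedure | Rejects |
|---|---|
| Friedman, arranged by condition | about 20% |
| Friedman, arranged by visit | about 96% |
| Gated rule, normal baselines | about 7% |
| Gated rule, skewed or clustered baselines | about 18%–19% |
| Fixed crossover test | about 5% |

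The gated figures use the arrangement by condition.

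**4. The branches are not interchangeable under an effect.** At d = 0.65, N = 20 and no drift, Friedman rejects in about 96% of runs and the fixed crossover test in about 78%. The higher figure is not a better test of treatment. Friedman rejects for any difference among the four conditions.

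**The case against.** **The screened quantity is not stated.** A reader might infer that the gate certainly acts on raw visit scores. The article does not support that as fact. It refers only to the outcomes, and it defines the primary one as a change. If change scores are screened, the participant's level cancels. In a three-cluster leg-score illustration a change score then fails in about 5% of trials (7% with rounding and score limits). This objection stands, and the 69% to over 99% figures are conditional on the visit-score reading. The 2 × 4 layout and four assessments make that reading plausible. A change from baseline is still not the active-minus-sham contrast, and the switch remains either way.

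**Type I error.** A reader might also infer that two-stage selection by itself pushes the error away from 0.05. The calculations do not show this: without drift it stays near 0.05. The excess needs a time trend, and the 0.5 error SD is an assumption. Some drift is plausible, since participants must be receiving physiotherapy and are assessed repeatedly.

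**The rule is written in advance.** Both branches and both screening tests are named, so this is not an unplanned choice. That is true. What is not fixed is which hypothesis will be tested.

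**Detail may sit in the analysis plan.** A fuller plan could say which variables are screened and how many failures count; nothing in the article says that eight cells are tested or that one failure is enough. It could not keep the stated rule and also fix a single primary test.

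**Conclusion.** The point holds as a defect in a stated rule, not as an omission. The primary hypothesis depends on a preliminary significance test, and one of the two possible analyses does not compare the randomised sequences, although the same section promises a comparison of the randomised groups.

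The firm part needs no simulation: two branches, different hypotheses, chosen after the data are seen. The frequency of switching rests on assumed distributions. It runs from about 8%–17% by chance with four tests (18%–32% with eight; correlation 0.80–0.985) to most trials if visit scores are screened in a heterogeneous sample. Type I error is not shown to be wrong in general. It is near 0.05 without drift and is not guaranteed when scores drift. The point should be corrected before analysis, but it does not invalidate the trial's design.

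**What to change.** In the Data analysis section:

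1. Delete the Shapiro–Wilk and Levene gate and the choice of test that follows from it.
2. Name one primary analysis and use it whatever the distribution: the within-participant active-minus-sham change in motor score, adjusted for period by comparing the two sequences. In the simulations this holds 4.4%–5.5% type I error.
3. Inspect residuals descriptively only.
4. As a stated supporting analysis, add the exact re-randomisation test of the same contrast over the sequence labels of the participants analysed. There are C(20,10) = 184,756 arrangements if all 10 + 10 are analysed and C(14,7) = 3,432 at 7 + 7, so the number must follow the actual completers. The test needs no normality and keeps the hypothesis unchanged.

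The cost is a few sentences of text and one small computation, with no new data or visits.
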